#### Comparison Cohort

We will identify a contemporaneous comparison cohort using administrative health data for a population not enrolled in the C2C program and who have an ED visit or hospital admission with an associated ICD-10 Z59x diagnosis (problems related to housing and economic circumstances) and at least one visit to a Calgary facility between 2014 and 2019. We will use propensity score matching to create a control group from this population. Propensity scores will be calculated for both the C2C and control cohorts and controls will be matched to C2C enrolled clients. This allows us to account for the covariates that may predict C2C enrolment, approximating random assignment and reducing selection bias between the groups. We will use a generalized linear modeling framework to estimate the effect of C2C enrolment on acute care utilization and death rates between these two groups.

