**Figure 1 F1:**
[figure not shown]
Program implementation and study timeline.

To be eligible for the program, patients must be ≥ 18 years of age, homeless or unstably housed (38), have ≥ 3 ED presentations, or ≥ 2 hospitalizations within the past year. While definitions of high acute care use vary, we chose the most conservative definition (18) in order to make the program inclusive and allow refinement to occur over the initial phases of implementation. Preliminary data gathered for the first 127 patients referred to the program before expansion indicates that, on average, C2C patients had 9 ED visits in the year prior to referral and 20% had a hospital admission. The most common reasons for admission were cellulitis, sepsis, pneumonia, substance use and other mental health diagnoses. C2C patients were more likely to be male (66%), 29% identified as Indigenous, 88% used substances and 78% were homeless. Referrals are accepted from acute care facilities, health clinics, and community agencies. Reasons for referral include attachment to primary care, housing support, connection to substance use treatment, advocacy, and discharge planning.

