### Structure and Process

We will document and describe the structure of C2C, as well as its processes and associated metrics. Structural elements include organizational supports, community partners, personnel, and IT infrastructure. Processes include team activities and operational procedures (e.g., program referrals and triage). Process metrics include referral numbers, engagement (i.e., patients who agree to work with C2C staff), enrolment status (i.e., active, graduated, lost to follow up, or deceased), housing stability, primary care attachment, and medication insurance acquisition. We will derive data primarily from meeting notes, program documentation, and team activity logs. To elicit further detail on structure and process, we will supplement with data from qualitative interviews and observations (see below).

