#### Power Calculation

We calculated power for the within-subject comparison for the primary outcome of ED visit rate over 12 months. Under ideal conditions intensive case management with outreach may reduce ED visits by 30% in high users (18). Assuming a mean pre-intervention rate of 9.3 visits/year (as noted for Phase 1 patients) and a post-intervention rate of 6.5 visits/year, a common standard deviation of 10, and a correlation between paired observations of 0.05, a sample of 257 individuals will provide more than 90% power to detect a difference at the 5% level of significance. Note that if the correlation increases, the power will increase, hence our choice of a low correlation. We have a waiver of consent to access administrative health data; therefore all patients that engage with the C2C team are eligible for inclusion in the administrative data analysis. Given our use of administrative data with full capture for participants in Alberta, any loss to follow up will be due to outmigration or invalid personal health insurance numbers. Despite this expected attrition, with 249 engaged patients in July 2018, by end of 2019, we will have an adequate study sample to detect meaningful differences.

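### Referred patients who never engaged can serve as matched controls, so the cohort comparison may partly set engagers against non-engagers

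*Protocol article*

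**What the plan says.** All places are in the protocol article.

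- **Comparison Cohort** defines the control pool as "a population not enrolled in the C2C program" with a Z59x-coded emergency visit or admission, plus some contact with a Calgary facility during 2014 to 2019. It then states that "controls will be matched to C2C enrolled clients". Of the matching it says: "This allows us to account for the covariates that may predict C2C enrolment, approximating random assignment and reducing selection bias between the groups". The outcomes are acute care utilization and death rates.
- **Structure and Process** lists referral numbers and engagement as separate metrics. It describes the latter as "engagement (i.e., patients who agree to work with C2C staff", and the next metric as "enrolment status (i.e., active, graduated, lost to follow up, or deceased". None of those statuses fits a referred patient who never agreed.
- **Power Calculation** says that "all patients that engage with the C2C team are eligible for inclusion in the administrative data analysis", and counts progress towards the sample in engaged patients (249 in July 2018).
- **The Connect 2 Care Intervention**, in the eligibility paragraph after Figure 1, says: "Referrals are accepted from acute care facilities, health clinics, and community agencies".

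Nothing in the article says how referred patients who did not engage are treated when the control pool is formed.

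**The concern.** The two groups are defined by different steps of the same pathway. Entry to the program group requires agreement; entry to the control pool requires only the absence of enrolment. People who were offered the program and refused, or who could not be found, drop out of the first group and become available to the second.

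Such people may differ from engagers in ways that affect emergency visits and mortality whether or not the program works: trust in services, stability, severity of substance use, being reachable at all. If they make up a noticeable part of the matched controls, the comparison reflects the difference between accepting and not accepting help as well as the effect of the program.

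What is at stake is the only one of the three quantitative approaches that has a concurrent unexposed group, and the only one whose description names death as an outcome.

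**Working it through.** **1. Group membership, set side by side.**

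| Patient | Program group? | Control pool? |
|---|---|---|
| Referred and agreed | Yes | No |
| Referred, declined or never reached, Z59x-coded | No | Yes, because not enrolled |
| Referred, declined or never reached, no Z59x code | No | No |
| Never referred, Z59x-coded | No | Yes |

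The second row is the problem. It follows from reading Comparison Cohort, Structure and Process, and Power Calculation together.

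**2. Can matching repair it?** The propensity score is built from administrative data. Willingness to engage is unlikely to be recorded there, so it cannot be balanced. Referral status is different: the program tracks referrals, so this part of the problem can be identified and avoided.

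**3. The plan's own figure.** The only power figure is for the within-subject comparison; none is given for the matched one. It reproduces:

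- difference 9.3 − 6.5 = 2.8 visits/year
- SD of the paired difference = 10 × √(2 × (1 − 0.05)) = 13.78
- power with 257 patients, two-sided 5% = Φ(2.8 / (13.78/√257) − 1.96) = 90.3%

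This does not bear on the group definitions. The 2.8 visits serve below only as a yardstick.

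**4. Possible size.** The article gives neither the engagement rate nor the outcomes of non-engagers, so everything here rests on assumptions. Let *f* be the share of matched controls who are referred non-engagers, and *r* their event rate relative to otherwise comparable unreferred people. With no program effect, and taking unreferred people as the proper comparator, the observed rate ratio is 1 / (1 + *f*(*r* − 1)).

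| *f* | *r* | Rate ratio with no effect |
|---|---|---|
| 10% | 1.2 | 1/1.02 = 0.98 |
| 20% | 1.5 | 1/1.10 = 0.91 |
| 30% | 2.0 | 1/1.30 = 0.77 |
| 20% | 0.8 | 1/0.96 = 1.04 |

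The last row shows that the sign reverses if non-engagers use less care.

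In visits, the control mean shifts by *f* × *D*, where *D* is the difference in visits/year between non-engagers and comparable unreferred people. For *f* from 5% to 30% and *D* from 1 to 5, the shift is 0.05 to 1.5 visits/year, or 2% to 54% of 2.8.

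**5. How large can *f* be?** If a share *e* of referred patients engage, there are 257 × (1 − *e*)/*e* non-engagers per 257 engaged:

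| *e* | 90% | 80% | 70% | 60% | 50% |
|---|---|---|---|---|---|
| Non-engagers | 29 | 64 | 110 | 171 | 257 |

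With one control per enrolled patient:

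- *f* = 10% needs about 26 non-engagers to be coded and matched. At 80% engagement that is 26/64, about 40% of them.
- *f* = 20% needs about 51: 51/64 = 80% of them at 80% engagement, 51/110 = 46% at 70%.
- *f* = 30% needs 0.3 non-engagers per enrolled patient, so *e* can be at most 1/1.3 = 77%, and at that limit every one must be coded and matched.

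With two controls per patient, *f* = 30% requires *e* of at most 1/1.6 = 62.5%.

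**The case against.** **The terms are loose.** Enrolled is never defined against engaged or referred. The Power Calculation sentence concerns the consent waiver and says who may be included, not who is left out. The eligibility paragraph also describes the first 127 referred patients as C2C patients. If enrolment meant referral, the point would weaken. It still stands as the better reading: engagement is described as agreement, the enrolment statuses have no place for someone who never agreed, and the sample is counted in engaged patients.

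**It may be a detail left to the full protocol.** An article need not give every exclusion. But this one states the pool definition and what matching is supposed to achieve, and it is that stated definition which admits non-engagers.

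**It is already conceded.** The Discussion accepts unmeasured confounding by variables absent from administrative data. That covers willingness to engage in general, but not the use as controls of people whom the program's own records could identify.

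**The direction is not established.** This stands. A reader might infer that the bias must favour the program. The Introduction does link distrust to reduced engagement and later, more severe acute presentation, which makes that direction plausible. But some non-engagers may already have other services or may have left the province, and nothing in the article settles the matter.

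**The amount may be small.** This also stands. Only Z59x-coded non-engagers enter a pool that spans several years of Calgary contacts. A reader might infer that matching will preferentially select them because they resemble enrolled patients; the article does not list the matching covariates, so that is conjecture.

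**Conclusion.** The point holds as a weakness in how the control pool is defined. Referred patients who declined or were never reached can serve as controls, and matching on administrative data cannot balance willingness to engage.

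The size is unknown. Under the assumptions shown, a program with no effect could give a rate ratio from 0.98 down to 0.77, or slightly above 1 if non-engagers use less care. The 0.77 scenario requires low engagement or near-complete coding and matching of non-engagers, and should not be read as an expected value.

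Two stronger readings are not supported:

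- **That the primary result is compromised.** The powered comparison of emergency visits is within-subject and has no control pool, though it too is limited to engagers.
- **That removing non-engagers from the pool would cure the comparison.** Never-referred controls still include people who would have declined, while the program group remains selected on agreement.

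The change is worth making because it is cheap and uses information the program already keeps.

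**What to change.** In Comparison Cohort:

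1. Exclude from the control pool anyone whom the program log shows was referred to C2C on or before that control's index date.
2. Do not censor controls at a later referral. Eligibility depends on acute care use and acute care facilities refer, so such censoring would be tied to the outcome.
3. Add a sensitivity analysis in which the exposed group is everyone referred, engaged or not, followed from the referral date and matched to people not referred by that date.
4. Describe the main matched result as an effect among engagers, and drop the claim that matching approximates random assignment.

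Costs: linking the referral log to the administrative data, possibly with an amendment to the consent waiver to cover referred patients who did not engage; a slightly smaller control pool; and a diluted estimate in the all-referred analysis. Some selection on agreement remains in the main matched comparison and should be acknowledged. No sample-size figure changes.

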#### Population-Level Analysis

Phased implementation provides an opportunity to examine trends in acute care use using administrative data for the target population as a whole. With increased reach of C2C in Calgary with each phase, the proportion of the target population exposed to C2C will increase over time, and, if successful, acute care use in this population will, on average, decrease over time. We will select a population of patients from administrative health data who present to a Calgary acute care facility and meet the following criteria: ≥ 18 years of age; ED visit or hospital admission with an associated ICD-10 Z59x diagnosis (problems related to housing and economic circumstances); ≥ 3 ED presentations, or ≥ 2 hospitalizations within the past year; and at least one high-risk health condition, as defined by ICD-10 diagnostic codes corresponding to C2C enrolment criteria.

Beginning 6 months prior to C2C program implementation, and continuing for 12 months beyond enrolment end date (i.e., May 2015–December 2020), we will retrospectively ascertain the following every 3 months: total number of patients meeting eligibility (per administrative data as above); proportion of patients currently or previously enrolled in C2C (per program data); acute care use for the prior 12 months. We will inspect the number of eligible patients enrolled in C2C over time to ensure our increased enrolment assumption is correct. We will use a generalized linear modeling framework to assess the trend over time, in both the total number of eligible patients in administrative data (to assess change in the absolute number) and average acute care use (to assess change in use among those who meet criteria), measured at 3-month intervals. We will adjust for age, sex and defined health conditions.

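### C2C patients qualify by housing status with no code required, while the control pool and the population series use any Z59x code, so the groups are not defined alike

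*Protocol article*

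**What the plan says.** **Program entry.** The eligibility paragraph in The Connect 2 Care Intervention states that "patients must be ≥ 18 years of age, homeless or unstably housed (38"), with a threshold of three ED presentations or two hospitalizations over the preceding year. Housing status rests on a cited definition, not on a diagnosis code. The same paragraph adds: "Referrals are accepted from acute care facilities, health clinics, and community agencies". Power Calculation makes every patient who engages with the team eligible for the administrative data analysis, again without a code.

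**Matched comparison.** Comparison Cohort draws controls from people not enrolled in C2C whose ED visit or admission carries "an associated ICD-10 Z59x diagnosis (problems related to housing and economic circumstances"). They must also have visited a Calgary facility at least once between 2014 and 2019. Controls are then matched to enrolled clients on a propensity score.

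**Population series.** Population-Level Analysis requires age 18 or over and "ED visit or hospital admission with an associated ICD-10 Z59x diagnosis (problems related to housing and economic circumstances); ≥ 3 ED presentations" or at least two hospitalizations in the past year, plus a high-risk condition. Each quarter it counts the "total number of patients meeting eligibility (per administrative data as above") and, among them, the "proportion of patients currently or previously enrolled in C2C (per program data").

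Neither analysis section names Z59 subcodes or adds a separate housing condition.

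**The concern.** The program defines its target group by housing. Two of the three effectiveness approaches define it by a code block that, on the article's own description, also covers economic problems. The mismatch runs in both directions.

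- **Too wide.** A person whose only Z59x code is economic satisfies the code rule whatever their housing. Such a person may not be eligible for C2C, yet can be drawn as a control or counted in the series.
- **Too narrow.** An enrolled patient with no Z59x code on an ED visit or admission is treated in the matched comparison but cannot appear in the population series, because program records only flag enrolment among people already selected by code.

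If housing status affects acute care use, the matched contrast mixes that effect with the program effect. In the series, people outside the target group dilute any fall in average use and add to the count of eligible patients. Referral widened to all four hospitals and to community agencies in Phase 2. The coded share of enrollees could therefore shift by phase, along the same time axis on which the trend is estimated.

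**Working it through.** **1. The definitions side by side.**

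| Group | Housing condition | Source |
|---|---|---|
| C2C patients | Homeless or unstably housed by a cited definition; no code | Program records |
| Control pool | Any Z59x code on an ED visit or admission | Administrative data |
| Population series | Any Z59x code, plus age, high use and a high-risk condition | Administrative data; program data only mark enrolment |

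The first row is neither contained in the other two nor contains them. Having a Z59x code cannot separate housing problems from economic ones among controls, since all controls have one. No propensity covariates are listed, so matching is shown neither to remove the difference nor to leave it.

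**2. The plan's own figure.** Power Calculation gives means of 9.3 and 6.5 visits per year, SD 10, correlation 0.05, n = 257 and a 5% level (taken as two-sided).

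- SD of the paired difference = 10 × √(2 × 0.95) = 13.78.
- Power = Φ(2.8 / (13.78/√257) − 1.96) = 90.3%, or 90.0% with the noncentral t.

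The stated power of more than 90% reproduces. It concerns the within-subject analysis, which uses no Z59x rule.

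**3. Illustration for the matched contrast.** The documents give neither of two needed inputs: e, the share of matched controls who are coded only for economic problems and are not unstably housed; and r, their ED rate relative to other controls. The plan states no power for this contrast, so the Power Calculation means and SD are borrowed, with 257 per group.

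- Control mean C = 9.3 × (1 − e) + 9.3 × r × e
- Estimated reduction = (C − 6.5)/C
- SE = 10 × √(2/257) = 0.882
- Power = Φ((C − 6.5)/SE − 1.96)

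| e | r | C | Estimated reduction | Bias, (9.3 − C)/SE | Power |
|---|---|---|---|---|---|
| 0 | – | 9.30 | 30.1% | 0 | 89% |
| 0.1 | 0.9 | 9.21 | 29.4% | 0.1 | 87% |
| 0.2 | 0.75 | 8.84 | 26.4% | 0.53 | 75% |
| 0.4 | 0.6 | 7.81 | 16.8% | 1.7 | 32% |

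**4. Illustration for the population series.** Assume a 30.1% effect on exposed patients, 30% of the target population exposed, equal baseline use, no effect on others, and a share q of the series outside the target group. The fall in mean use is 0.301 × 0.30 × (1 − q): 9.0%, 8.1%, 6.8% and 4.5% for q = 0, 0.10, 0.25 and 0.50.

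Without equal baseline use, the relative fall is multiplied by (1 − q)/(1 − q + q × r). With q = 0.4 and r = 0.6 this is 0.6/0.84 = 0.71. The factor for the absolute fall stays at 0.6.

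Losing uncoded C2C patients lowers the exposed share further only if enrollees are coded less often than the rest of the target population. If coding is equally incomplete in both, the exposed share is unchanged but the series covers fewer enrollees.

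**The case against.** Several objections limit how far the point goes.

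- **Condensed article.** The exact code list and the propensity covariates may sit in a fuller document. But the article does state a rule, twice, with a description that includes economic circumstances. For high-risk conditions it says the codes correspond to C2C enrolment criteria; it says nothing similar for housing.
- **Code and housing status.** A reader might infer that anyone with an economic-only code is stably housed and could never be exposed to C2C. The documents do not support this. A code records what was noted at a visit, and the definition of unstable housing is given only by citation. Only that some such people may not be unstably housed can be said.
- **Role of housing.** A reader might also take housing as the main driver of acute care use. The Introduction ranks no drivers and names poverty beside homelessness as a barrier to care. Economically coded controls may therefore differ less than feared.
- **Matching.** That matching fails is not shown. If prior ED use is a covariate, r should move toward 1 and the bias shrink.
- **Uncoded enrollees.** Early C2C patients averaged 9 ED visits in the prior year, each a chance to be coded, so community referral does not imply a missing code. The plan will also inspect enrolment among eligible patients over time, a partial check.
- **Sensitivity against specificity.** Simply replacing Z59x with housing subcodes would drop more C2C patients from the series. This stands, and is why both definitions should be run.

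The Discussion concedes confounding by variables absent from administrative data. That general caveat does not name this mismatch, which arises from how the available codes are used.

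**Conclusion.** The mismatch in definitions holds on the text. C2C patients enter by housing status without a code; controls and the population series enter by a code block that also covers economic problems. Two of the three complementary approaches are affected.

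Its size cannot be determined from the documents. The range of estimated reductions, 29.4% to 16.8% against a true 30.1%, rests entirely on assumed e and r and on inputs borrowed from the within-subject calculation. It runs from negligible to material. The worst case supposes that, after matching, 40% of controls still use the ED 40% less, which is demanding. The direction (hiding a benefit) also depends on r being below 1, which is assumed.

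A reader might infer that the primary result is compromised. It is not: the within-subject analysis and its stated power do not use the Z59x rule. The point bears on whether the matched and population estimates can be read as describing the C2C target group, and it merits a change because the remedy is cheap.

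**What to change.** **Comparison Cohort.** Keep the full-Z59x matched analysis. Beside it, add one in which C2C patients and controls meet the same coded housing rule: a listed set of Z59 subcodes for homelessness or inadequate or unstable housing, recorded on or before the index date.

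**Population-Level Analysis.** Run the series under both the full Z59x block and the housing-subcode definition. Report by phase the share of C2C enrollees who meet each definition, and limit the interpretation to that share.

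**Cost.** A code list, one further matched analysis and a second run of the series, on data already being extracted. The control pool will be smaller and fewer C2C patients will contribute to the like-for-like analyses; showing both versions makes that trade-off visible.

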### The Connect 2 Care Intervention

C2C is a multidisciplinary mobile outreach team that provides transitional case management, advocacy, and care navigation for socially vulnerable patients. Clinical and operational leadership at CUPS developed the C2C pilot, launched with two registered nurses (RNs) in November 2015, in partnership with Foothills Medical Center, the largest of four tertiary care hospitals in Calgary. With innovation grant funding, we expanded the program across three implementation phases (see Figure 1). In Phase 1 (January–December 2017) two HNs were added; in Phase 2 (January–December 2018) the referral base expanded to all four Calgary hospitals, as well as community agencies, using two additional HNs; in Phase 3 (January–December 2019), the program reached maturity with 2 RNs and 4 HNs. HNs are hired from a pool of emergency shelter outreach workers at Calgary Alpha House Society, a housing, shelter, outreach, and detoxification facility. HNs are acquainted with the target population's social and community context and are provided health and health system navigation training. Collectively, the C2C team has expertise in chronic disease management, mental health, harm reduction and addictions, as well as extensive knowledge of social programs, community health, housing, financial and transportation resources.

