### Measures of Effectiveness

#### Acute Care Use

We will use administrative health data to assess acute care use among C2C patients 12-months before and after enrolment: ED visits (primary outcome); hospital admissions; repeat ED visits within 72 h of discharge; unplanned readmissions within 30 days among hospitalized patients; total hospital bed days; deaths; ED and hospital discharge diagnoses; and ICU admissions. Data will be obtained by linking unique provincial health insurance numbers to administrative health data housed by Alberta Health Services.

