### Quantitative Data Analysis

Given the complexity of the intervention, selecting a comparison group is inherently complex. To provide statistical estimates for effectiveness, we will consider three complementary approaches: (1) a within-subject controlled analysis, (2) comparison to a cohort of similar patients, and (3) a population-level analysis assessing use of healthcare services over time. While each has interpretive caveats, they provide complementary perspectives, and together provide a clearer indication of the impact of C2C.

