## Discussion

The proposed study has some limitations. First is the absence of a randomly allocated comparison group. The use of propensity score matching to create a control group will help to reduce bias but unmeasured confounding by variables that are not available in administrative health data may occur. Second, the nature of our study population may lead to challenges in locating and connecting with patients for interviews and follow-up. Therefore, we may not capture the unique experiences of patients facing additional barriers that impact ability and willingness to connect. Our follow-up period also limits our ability to determine whether outcomes persist or new outcomes arise past 12 months post-enrolment. However, a longer follow-up period would create additional challenges in connecting with patients and increase bias within our results. Third, results might be influenced by time-varying confounders unrelated to C2C, such as natural changes in health. Finally, our evaluation occurs within the context of a single city which reduces generalizability, thus careful consideration should be given to the local context when applying evaluation findings across settings.

Despite these limitations, our study has several advantages. A main advantage is our mixed-methods approach, which examines the impact of the program both quantitatively, across multiple outcomes, and qualitatively. Our qualitative data include observations and interviews with multiple stakeholder groups. Integration of data across multiple sources will ensure that valuable patient, staff, and partner perspectives are considered. As our evaluation occurs within the context of the C2C program, results will also reflect patient and program outcomes in a real-world setting. Thus, results will directly inform decisions on C2C and related interventions.

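### The control rule does not place the qualifying Z59x encounter in Calgary, so the matched pool can include people who mainly use another city's services and could not have been referred to C2C

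*Protocol article*

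**What the plan says.** The Quantitative Data Analysis section lists three complementary approaches, the second being "comparison to a cohort of similar patients". The Comparison Cohort section defines the source population as people not enrolled in C2C "who have an ED visit or hospital admission with an associated ICD-10 Z59x diagnosis" "and at least one visit to a Calgary facility between 2014 and 2019". Propensity score matching then draws the control group from that population. The article does not list the covariates in the score.

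Three other places bear on this:

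- **Data.** Acute care use comes from "linking unique provincial health insurance numbers to administrative health data housed by Alberta Health Services", and the Power Calculation section adds: "Given our use of administrative data with full capture for participants in Alberta". The source is the province, not the city.
- **How patients reach C2C.** The intervention section describes a pilot launched in November 2015 with one Calgary hospital. In 2018 "the referral base expanded to all four Calgary hospitals, as well as community agencies".
- **Setting.** The Discussion states that "our evaluation occurs within the context of a single city" and asks for care over local context when findings are applied elsewhere.

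**The concern.** A matched control should stand for what would have happened to a C2C patient without C2C. That person should have been reachable by the program and should have received Calgary's usual care. The stated rule secures neither. Its two conditions are separate, and only the second mentions Calgary. Someone who is homeless in another Alberta city, was given a Z59x code there, and attended a Calgary facility once in 2014 meets both.

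This matters because the matched cohort is the only one of the three approaches with an external control at patient level. It is the main check on the changes over time that the within-subject analysis cannot separate from the program. If some controls spend their follow-up year under another city's ED access, shelter and housing services, a difference between cities is counted as an effect of C2C.

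**Working it through.** **1. Reading the rule.** If the Z59x encounter already had to be in Calgary, a further requirement of one Calgary visit would add little beyond the date window. The natural reading is that the Z59x encounter may be anywhere in the data, and the data are Alberta-wide.

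**2. The date window.** 2014 to 2019 is six calendar years, or 72 months. The pilot launched in November 2015, so January 2014 to October 2015, 12 + 10 = 22 months, precede any C2C service. A single Calgary visit in those 22 months satisfies the second condition. Referral from all four Calgary hospitals began only in 2018.

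**3. The plan's own figures.** The only sizing is for the within-subject comparison: 9.3 against 6.5 visits per year, SD 10, correlation 0.05, N = 257.

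- Planned reduction: (9.3 − 6.5)/9.3 = 2.8/9.3 = 30.1%.
- SD of the paired difference: 10 × √(2 × 0.95) = 13.784. Standard error: 13.784/√257 = 0.860.
- Power, two-sided 5% (sidedness assumed), normal approximation: Φ(2.8/0.860 − 1.96) = 90.3%.

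The stated power of more than 90% reproduces. It does not bear on this point, and no size or power is stated for the matched contrast.

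**4. Illustration of size.** Let g be the share of matched controls based outside Calgary. Let d be the relative difference in their follow-up ED rate, compared with Calgary controls, that remains after matching. Neither is in the documents; both are assumptions. Take 9.3 as the follow-up rate of Calgary controls (also an assumption, since the plan gives it as a pre-enrolment rate) and 6.5 for C2C. Then

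apparent reduction = 1 − 6.5 / (9.3 × (1 + g·d)).

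| g | d | Control mean | Apparent reduction | Shift from 30.1% (points) |
|---|---|---|---|---|
| 0.1 | −0.4 | 8.93 | 27.2% | −2.9 |
| 0.1 | +0.4 | 9.67 | 32.8% | +2.7 |
| 0.2 | −0.4 | 8.56 | 24.0% | −6.1 |
| 0.2 | +0.4 | 10.04 | 35.3% | +5.2 |
| 0.3 | −0.3 | 8.46 | 23.2% | −6.9 |
| 0.3 | +0.3 | 10.14 | 35.9% | +5.8 |
| 0.3 | −0.15 | 8.88 | 26.8% | −3.3 |
| 0.3 | +0.15 | 9.72 | 33.1% | +3.0 |

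The last two rows show the 30% difference with half of it absorbed by matching. If C2C had no effect, g = 0.3 with d = +0.3 would by itself give an apparent reduction of 1 − 1/1.09 = 8.3%. With d = −0.3 it would give an apparent increase of 1/0.91 − 1 = 9.9%. If g = 0 or d = 0, the bias is nil.

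**The case against.** The strongest reply is that this rule defines a source pool, not the control group. Matching follows, on covariates that predict enrolment, and being in Calgary is an obvious predictor of enrolment in a Calgary program. A reader might infer from the article that place has been left out of the score. It does not show that: it lists no covariates at all, and that list is commonly left to a fuller document. If place is in the score, most of the problem goes.

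A second reply also has force. A stable difference between cities in ED access would already show in prior-year use, so matching on prior use would absorb much of it. What remains is mainly change from one year to the next that differs by city. That is why d above is defined as the difference left after matching.

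Third, the article calls the cohort contemporaneous, and a window opening in 2014 may be meant to supply pre-enrolment history. The stated rule does not say so.

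Fourth, this is one of three analyses offered with caveats, and not the one that was sized. The Discussion concedes residual confounding after matching, but only by variables missing from administrative data. Facility location is not missing, because the rule itself uses it.

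A reader might also infer that the Population-Level Analysis is stricter on place. It says "We will select a population of patients from administrative health data who present to a Calgary acute care facility and meet the following criteria", and the Z59x encounter is then one listed criterion with no location. On place the two sections have the same structure, so no contradiction between them is shown.

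**Conclusion.** The point stands as a weakness in a stated selection rule. The rule permits a between-city difference in the matched contrast that is easy to avoid. The matched comparison should be tightened; the within-subject primary analysis is untouched.

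The documents do not support going further. No bias is demonstrated, because the share of matched controls based elsewhere and their relative ED use are unknown. The direction is open, so it cannot be said that the rule flatters or hides the effect of C2C, or that it costs power. Under the assumed values the shift runs from under 3 points (10% based elsewhere, difference up to 40%) to about 7 points (30% based elsewhere, difference 30%), and less if prior use or place is matched.

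A reader might conclude that controls should have to live in Calgary. The documents do not support that remedy: the eligibility criteria state no residence test for C2C patients, and 78% of the first 127 referred were homeless, so recorded residence is a doubtful anchor.

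**What to change.** In the Comparison Cohort section, make two changes:

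1. Require that the Z59x-coded ED visit or admission that makes a control eligible (the index encounter) took place at a Calgary facility within the C2C enrolment period. This replaces the condition of one Calgary visit in 2014–2019. Earlier data can still be used for prior-year history.
2. Include in the propensity score the share of prior-year acute visits made at Calgary facilities, computed in the same way for C2C patients and controls. State how a person with no prior-year acute visit is handled, since the share is then undefined.

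The selection rule already relies on identifying Calgary facilities, so no new data source should be needed. The cost is one changed selection line, one added matching variable and a somewhat smaller control pool.
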